## University of Naples “Federico II” - Naples, Italy

Components, hierarchical clustering, Analysis of the Main Coordinates, etc.) will be used to identify possible groupings of the samples and the variables that allow to explain these subdivisions. All statistical tests will be carried out in the R / Bioconductor environment and using specific software (stats, vegan, made4, rgl, etc.). The relative abundance tables of the microbial species will also be used for correlation analysis with the other quantitative variables available using the psych software in the R environment. The level of significance for all statistical tests will be 2-sided,  $p < 0.05$ . When appropriate, all significance values will be corrected to take into account the effect of multiple comparisons, using the Bonferroni correction. All data were collected in a dedicated database and analyzed by a statistician blinded to patient group assignment, using SPSS version 19.0 for Windows (SPSS Inc, version 14.0, Chicago, IL).

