## University of Naples “Federico II” - Naples, Italy

### *Population*

#### **Inclusion criteria**

Children/adolescents with diagnosis of obesity (BMI >95° percentile for age and sex), 5-17 years, observed at Pediatric Section of Department of Translational Medical Sciences (University of Naples Federico II).

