## University of Naples “Federico II” - Naples, Italy

### *Study Design*

Quadruple-Blind Randomized, Monocentric, Placebo-controlled Study.

Obese patients related to the Pediatric Section of Department of Traslational Medical Science of the University of Naples "Federico II" will be evaluated for the study.

At the baseline, inclusion and exclusion criteria will be assessed and the aims and methods of the study will be illustrated to parents/tutors and young patients. After obtaining informed consent from the patients and their parents/tutor (Annex 1.), patients will be enrolled and randomly assigned to two group of 6-month intervention.

Group 1: standard care for pediatric obesity + sodium butyrate (20 mg/kg body weight/day)

Group 2: standard care for pediatric obesity + placebo (cornstarch)

The packaging, color, weight, smell and taste of the active product and of the placebo will be identical without indication of group identity or content and will be labeled with a serial number according to the computer-generated randomization list, and thus ensured blind conditions.

Instructions for keeping and maintaining the product will be also providing.

All study subjects will be evaluated by a multidisciplinary team (composed by pediatricians, nutritionists and pediatric nurses experienced in the care of pediatric obesity).

Anamnestic, demographic, anthropometric and clinical data will be

[figure not shown]

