## University of Naples “Federico II” - Naples, Italy

collected and reported in a specific clinical chart ([Annex 2.](#)).

The patients and their parents/tutor will be instructed on how to complete a food record ([Annex 3.](#)) for the evaluation of dietary patterns which will subsequently be analyzed by a specific software (Winfood - Medimatica Srl). Compliance with the recommendation regarding physical activity and sedentary behaviors at T6 was assessed by questioning about lifestyle habits ([Annex 4.](#)).

At enrollment (T0) and every month for 6 months (T1, T2, T3, T4, T5, T6) will be evaluated: body weight, height, BMI, weight for age percentile, height for age percentile, BMI for age percentile, waist circumference, blood pressure, eating behavior (3 days food record).

At the baseline (T0) and at the end of the study (T6) peripheral blood sampling will be performed for the evaluation of fasting blood glucose, basal insulin, HOMA-IR index, triglyceride, HDL cholesterol, LDL cholesterol, total cholesterol, ghrelin, and expression profile from PBMCs of miR-221. At enrollment (T0), before the start of interventions, and after 6 months (T6) a stool sample for each patient (3 g) will be collected for the metagenomic analyses of the gut microbiota. All samples will be collected from diapers in sterile plastic tubes and stored at -80°C until analysis.

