## University of Naples “Federico II” - Naples, Italy

### **Sample size**

Considering a possible drop-out of 10%, will be required 27 patients per group (Group 1: n=27; Group 2: n=27) to observe a BMI z-score reduction at least of  $\geq 0.25$  after 6 months of intervention (Power of the study 90%; type 1 error =0.050, 2- tailed test).

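### The species correlations are planned without a stated age adjustment in children aged 5 to 17, so a species that varies with age may appear linked to raw weight, height, BMI or waist when no direct link exists.

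*Protocol*

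**What the plan says.** The Statistical analysis section of the protocol plans that "The relative abundance tables of the microbial species will also be used for correlation analysis with the other quantitative variables available". The R package named for this is psych. The section names no covariate, partial correlation, time point or handling of the two arms.

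Three other places bear on it:
- Inclusion criteria set the age range: "Children/adolescents with diagnosis of obesity (BMI >95° percentile for age and sex), 5-17 years".
- The visit schedule under Study Design supplies the quantitative variables, which mix raw and age-standardised measures: "body weight, height, BMI, weight for age percentile, height for age percentile, BMI for age percentile, waist circumference, blood pressure".
- Stool is taken twice: "At enrollment (T0), before the start of interventions, and after 6 months (T6) a stool sample for each patient (3 g) will be collected".

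The same Statistical analysis section separately plans a generalized linear model for how demographic, anamnestic and clinical data contribute to microbiota composition. It also plans a Bonferroni correction where appropriate, without a number of tests.

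**The concern.** Between 5 and 17 years, raw weight, height, BMI and waist all rise with age. If a species' abundance also varies with age, age is a common cause, and the two will correlate even if neither has anything to do with the other at a given age. A correlation matrix of species against every quantitative variable would list such pairs beside any genuine ones, and nothing in the stated method separates them.

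The gut microbiota is a listed secondary outcome, and species-host associations are a likely reported result. What is at stake is the reading of those associations: some could describe how old a child is rather than how the microbiota relates to adiposity.

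The two arms can act in the same way after treatment. If butyrate moved both a species and a marker, the two would correlate across the pooled children at T6 even if unrelated within each arm.

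**Working it through.** **Inputs from the protocol.** The Sample size section states that "will be required 27 patients per group (Group 1: n=27; Group 2: n=27", so N = 54. With the stated 10% dropout, 54 × 0.9 = 48.6, or about 48 completers (24 per arm). Tests are two-sided at 0.05. The protocol gives no figure for the correlation analysis, so there is nothing of its own to reproduce here; the sample size enters only as N.

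**Inputs assumed.** The documents contain no correlation with age. I take species-age r of 0.2, 0.3 and 0.4, and variable-age r of 0.65, 0.75 and 0.95 to span the raw measures (BMI lowest, height and weight highest). Age is uniform over 5-17. There is no direct species-variable link.

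**Step 1: induced correlation.** With age as the only connection, r(species, variable) = r(species, age) × r(variable, age). The range runs from 0.2 × 0.65 = 0.13 to 0.4 × 0.95 = 0.38.

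**Step 2: chance of p<0.05.** By Fisher's z, this is about Φ(atanh(r) × √(N − 3) − 1.96), with √51 = 7.141.
- r = 0.13: 0.131 × 7.141 = 0.93, and 0.93 − 1.96 = −1.03, which gives 15%.
- r = 0.3 × 0.95 = 0.285: 0.293 × 7.141 = 2.09, and 2.09 − 1.96 = 0.13, which gives 55%.
- r = 0.38: 0.400 × 7.141 = 2.86, and 2.86 − 1.96 = 0.90, which gives about 81%.

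**Step 3: simulation.** Rank correlation, 20,000 runs per cell, N = 54, share with p<0.05:

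| Variable-age r | Species-age 0.2 | 0.3 | 0.4 |
|---|---|---|---|
| 0.65 | 15% | 28% | 47% |
| 0.75 | 18% | 37% | 60% |
| 0.95 | 27% | 53% | 81% |

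Adjusted for age, every cell returns to about 5%. At N = 48 the last row is 24%, 49% and 76%.

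**Step 4: variables little affected.** BMI z-score, assumed unrelated to age, stays at 5% without adjustment. Insulin, assumed weakly related to age, gives 6%, 9% and 11% across the three species-age values.

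**Step 5: Bonferroni.** The number of tests is not given, so two values are assumed.
- 400 tests (nominal 0.05/400 = 0.0125% per test), variable-age r 0.65-0.93: the rate is 0.2-0.6% at species-age 0.2 and 2-13% at 0.4.
- 100 tests (nominal 0.05%), variable-age r 0.75-0.95: the rate is 10-24% at species-age 0.4.

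The rates are much lower, but still above nominal.

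**Step 6: arms pooled at T6.** If treatment shifts species and variable by d SD each, with no link within arms, the pooled r = (d²/4)/(1 + d²/4). With 24 per arm:
- d = 0.5: 0.0625/1.0625 = 0.06, rejection 7%.
- d = 0.7: 0.1225/1.1225 = 0.11, rejection 11%.
- d = 1: 0.25/1.25 = 0.20, rejection 28%.
- d = 1.5: 0.5625/1.5625 = 0.36, rejection about 76%.

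**The case against.** The best reply is that the protocol does not say the correlations are unadjusted or pooled, and that such detail of an exploratory analysis often sits in a SAP. That is partly right: unadjusted and pooled are both read from the absence of any qualifier. But the sentence does fix a method, its data and its software, and where the section wants covariates it asks for a model. Carried out as written, it gives age-confounded results for the raw measures.

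A second reply points to the generalized linear model. It is a separate analysis of microbiota composition, does not name age, and adjusts nothing in the correlations, which are additional to it. It does mean that the correlations are not the only planned route from microbiota to clinical data.

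A third is that a species-weight correlation arising through age is a real marginal association, so the test is not invalid. True; the harm lies in reading it as a link beyond age.

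A reader might infer more than the documents support:
- *That any age-related species will appear linked.* At species-age r = 0.2, about three quarters or more of such species would miss p<0.05 for a given variable, and more would under Bonferroni.
- *That the metabolic outcomes are heavily affected.* The large rates belong to raw anthropometry. Of the metabolic markers only insulin was examined, at 6-11%. The age-standardised percentiles on the same list are largely protected.
- *That the two arms distort every correlation.* T0 stool precedes treatment, so only T6 values or changes are exposed, and the effect is small below shifts of about 0.7 SD in both quantities.

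**Conclusion.** The point holds in limited form. The protocol plans species correlations with all other quantitative variables and states no age adjustment, in a sample spanning 5-17 years. For raw weight, height, BMI and waist, a species that varies with age may be declared linked at p<0.05 in roughly 15-80% of cases rather than 5%, at N = 54. That range rests wholly on the assumed species-age (0.2-0.4) and variable-age (0.65-0.95) correlations and a uniform age spread; a narrower age mix would lower it. Bonferroni reduces the rate without restoring the nominal level. Arm confounding is conditional on T6 or change data and on a substantial treatment effect on both quantities.

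This concerns a secondary, exploratory analysis. The BMI z-score comparison between the arms is not affected. The change is worth making but is not critical to the trial's main conclusion.

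**What to change.** Replace the correlation sentence in the Statistical analysis section with wording such as: *Associations between species and quantitative variables will be partial rank correlations adjusted for age and sex, and also for randomised arm when T6 values or T0-T6 changes are used. BMI z-score will be used in place of raw body weight, height and BMI.* Waist can stay in the list, since it is then age-adjusted.

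The cost is one sentence and a few lines of R. No new data are needed: age, sex and arm are available for every child. The statistician is to be blinded to group, and a coded arm label is enough for the adjustment. The loss is up to 3 degrees of freedom. By Fisher's z with N = 54 and a true r of 0.4 (atanh = 0.424), power goes from Φ(0.424 × √51 − 1.96), about 86%, to Φ(0.424 × √48 − 1.96), about 84%.

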### **Statistical analysis**

The Kolmogorov-Smirnov test will be used to determine whether variables will be normally distributed. For continuous variables the study groups will be compared using the mean equality test or, if necessary, the Mann-Whitney U test. The Kruskal-Wallis H-test will be used to compare the two groups. The comparison between two groups and between two samples will be performed using Welch's t test and Fisher's exact test respectively (with Bonferroni's correction). The  $\chi^2$  test and Fisher's exact test will be used for categorical variables. The data obtained will be assessed by means of linear logistic regression analysis in order to evaluate the possible influence of dietary factors and other variables (anthropometric data, glucose and lipid metabolism variables). We will use a generalized linear regression model (GLM) to examine the contribution of demographic, anamnestic and clinical data of children enrolled on the composition of the microbiota. A GLM model will be built and validated using the rms and ResourceSelection packages implemented in R respectively (<http://www.r-project.org/>). Multivariate statistical analysis (Analysis of the Main

[figure not shown]

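### The sample size assumes an uncorrected two-sided 0.05, but the analysis text attaches Bonferroni to the two-group test without saying whether the primary comparison is exempt or how many tests count

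*Protocol*

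**What the plan says.** Protocol, Main study outcome, names one main outcome: reduction in BMI z-score. Secondary study outcomes names ten laboratory measures: glycemia, insulinemia, HOMA, total cholesterol, LDL, HDL, triglycerides, ghrelin, IL-6 and miR-221. It adds dietary and lifestyle habits and gut metagenomics.

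Protocol, Sample size, gives the enrolment: "Considering a possible drop-out of 10%, will be required 27 patients per group (Group 1: n=27; Group 2: n=27". Power is 90%, with "type 1 error =0.050, 2- tailed test". No multiplicity adjustment enters this calculation.

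Protocol, Statistical analysis, makes three statements that bear on the threshold:

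- Continuous variables are compared between groups by a test of equal means or, if necessary, Mann-Whitney. No correction is mentioned there.
- A later sentence assigns the comparison of two groups and of two samples to "Welch's t test and Fisher's exact test respectively (with Bonferroni's correction". The bracket carries no condition and no exemption.
- At the end of the section, two-sided p < 0.05 is set for all tests, followed by a rule that, when appropriate, "all significance values will be corrected to take into account the effect of multiple comparisons, using the Bonferroni correction".

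No sentence lists the comparisons that Bonferroni covers, gives their number, or says whether the primary is among them.

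**The concern.** The primary analysis compares a continuous variable between two groups. On its face, the sentence that pairs the two-group Welch test with Bonferroni covers it. The sample size was calculated as if it did not. Both cannot hold unless the number of comparisons is one.

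The closing rule does not resolve this. The words that make it conditional give no criterion, so the threshold for the main result could be 0.05 or 0.05 divided by an unstated number. A primary p-value of 0.02, for example, would be significant with one or two tests counted (0.05/2 = 0.025) and not with five (0.05/5 = 0.010). Under the stricter reading, the trial is also smaller than its power statement implies.

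**Working it through.** **Inputs**

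- From Sample size: 27 per group, 10% dropout, two-sided 0.05, power 90%, reduction of at least 0.25.
- Not stated: the SD of the BMI z-score change, and whether 0.25 is a difference between groups. The effect is therefore back-solved from the stated 90%, which takes the protocol's power claim at face value.
- Not stated: the number of comparisons, k. A range is shown.

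**Step 1. The protocol's own figure.** Dropout: 24/(1 − 0.10) = 26.7, rounded up to 27, which agrees with the protocol and implies 24 evaluable per arm. The 90% cannot be reproduced independently without an SD. For a two-sample t test with n = 24 per arm (df = 2n − 2 = 46), 90% power at two-sided 0.05 requires a standardised difference d = 0.956. If 0.25 is the between-group difference, the implied SD is 0.25/0.956 = 0.26 (0.27 under the normal approximation).

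**Step 2. Power if the primary is tested at 0.05/k.** Noncentrality = d × √(n/2) = 0.956 × √12 = 3.31. Power is the probability that a noncentral t with 46 df exceeds, in absolute value, the critical value for two-sided 0.05/k. The normal approximation is Φ(3.2415 − z(1 − 0.025/k)), where 3.2415 = 1.9600 + 1.2816. In that form the loss depends only on k once 90% at 0.05 is granted.

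| k | Threshold | Power, noncentral t | Power, normal |
|---|---|---|---|
| 1 (primary exempt) | 0.0500 | 90.0% | 90.0% |
| 2 | 0.0250 | 83.6% | 84.1% |
| 5 | 0.0100 | 73.1% | 74.7% |
| 11 (primary + 10 laboratory outcomes) | 0.0045 | 62.9% | 65.7% |
| 20 | 0.0025 | 54.9% | 58.6% |

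Back-solving with all 27 per arm evaluable barely changes this: 63.2% at k = 11 (t).

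**Step 3. Size needed to keep 90% at k = 11.** z(1 − 0.025/11) = 2.838. Required n = 24 × [(2.838 + 1.2816)/3.2415]² = 38.8, so 39 evaluable per arm. Then 39/0.90 = 43.3, so 44 enrolled per arm, against 27 planned. The t calculation gives 40 evaluable and 45 enrolled.

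**The case against.** The strongest defence is that the protocol leaves the primary at 0.05 on an ordinary reading. There is one main outcome, two groups and one 6-month assessment in the sample size, so the primary comparison has no multiplicity to correct. The closing rule applies only when appropriate. The significance level for all tests is p < 0.05, matching the sample size. The earlier sentence on continuous variables offers an uncorrected test of equal means that could be the one meant for BMI z-score. All of this stands, and it is why the text cannot be said to require a corrected primary. It is still an inference: the bracket after the Welch test has no such qualifier, and nothing says which sentence governs the primary.

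A reader might infer that power as written is about 63%. The documents do not support that. They give no number of comparisons, and 63% is only the case of 11. A family of 11 leaves out the dietary, lifestyle and microbiota outcomes, so it is one illustration among several. The effect size is also back-solved, so the table shows what any test of this size with 90% power loses at a smaller threshold. It does not reveal an arithmetical error in the protocol.

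It may also be said that the family of tests belongs in a statistical analysis plan. That is fair for the detail of the secondary family. It does not dispose of the point, because the protocol already states a correction, attaches it to the two-group test, and sizes the trial without it.

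Finally, Bonferroni is a valid method for the secondary outcomes. Preferring Holm is an improvement in power, not the correction of an error.

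**Conclusion.** The point holds as an unresolved inconsistency between Sample size and Statistical analysis. The primary threshold is uncorrected in the first. In the second it is open to correction over an unstated number of tests. If the primary is exempt, the stated 90% stands. If it is not, the 90% fails even at two tests (about 84%), and is about 73% at five, 63% at eleven and 55% at twenty. These figures assume 24 evaluable per arm and a two-sample comparison, and they accept the stated 90% at 0.05 in place of the missing SD.

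Two stronger claims should not be drawn. Inflated false-positive rates from uncorrected secondary tests cannot be charged to this protocol, because it plans a correction. Nor do the documents give what would be needed to calculate how little Bonferroni would leave detectable in the species-level analyses. The change is worth making because the choice could decide the main result and costs almost nothing to settle.

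**What to change.** In Statistical analysis:

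1. State that the between-group comparison of BMI z-score reduction at 6 months is the single primary test, at two-sided 0.05 without multiplicity correction. Keep reduction as the outcome, as in Main study outcome and Sample size; a value at T6 would be a different endpoint.
2. Delete the bracketed Bonferroni after the Welch test as it applies to the primary.
3. Define the secondary family as the ten named laboratory outcomes and test it with Holm in place of Bonferroni. Holm gives the same family-wise control and is never less powerful. Replace the conditional closing rule with this definition.
4. Label the species-level and correlation analyses exploratory. False-discovery control there is optional; it trades family-wise control for power.

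If the sponsor does intend to correct the primary, the number of tests must be stated and the trial sized at the corrected level: about 44 to 45 enrolled per arm for eleven tests, on the assumptions above.

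Items 1 to 4 change wording only and leave the 27 per group as it is.

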### **Secondary study outcomes**

- To evaluate glucose metabolism parameters (glycemia, insulinemia, HOMA Index), lipid metabolism parameters (total cholesterol, LDL, HDL and triglycerides), serum levels of the hormone ghrelin and of the proinflammatory cytokine IL-6, and on the expression of microRNA-221;
- To assess dietary and lifestyle habits;
- To assess metagenomic characteristic of the gut microbiota.

[figure not shown]

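### Bonferroni is the only multiplicity correction named; it is valid but needlessly insensitive for the species-level microbiota tests, and false-discovery-rate control would be a cheap improvement (low priority).

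*Protocol*

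**What the plan says.** Metagenomics is a secondary outcome: "To assess metagenomic characteristic of the gut microbiota" (Protocol, Secondary study outcomes).

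The Statistical analysis section plans a generalized linear model for microbiota composition, then ordination and clustering. It adds a species-level screen: "The relative abundance tables of the microbial species will also be used for correlation analysis with the other quantitative variables available".

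On error control, the same section says "The level of significance for all statistical tests will be 2-sided", at 0.05, and continues that, where this is appropriate, "all significance values will be corrected to take into account the effect of multiple comparisons, using the Bonferroni correction". Earlier it attaches the same method to the group comparisons ("with Bonferroni's correction"). No other correction appears. The section does not say which tests form a family or when correction is appropriate, and it gives neither the number of species nor the number of tests.

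**The concern.** Bonferroni controls the chance of even one false positive in the family. That suits a few confirmatory claims. A screen of many species against many clinical variables aims to produce a list of leads, and what matters there is the share of false leads on the list. Family-wise control over hundreds or thousands of tests in a trial of this size will miss many moderate associations, so a species that is not significant could not be read as unrelated to the variable.

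A smaller point applies to the blood outcomes. If they are corrected as a family, Holm controls the same error rate as Bonferroni and never rejects less.

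**Working it through.** **Figures in the plan.** The protocol gives no power for the microbiota analyses, so there is none to reproduce. The sample size ("Considering a possible drop-out of 10%, will be required 27 patients per group") concerns BMI z-score and states no standard deviation; it is used here only for the number of evaluable children.

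**Inputs**
- Evaluable children: 2 × 27 = 54; 54 × 0.9 = 48.6, taken as 48 (24 per arm).
- Quantitative variables in the Annex 2 chart: nine body measures (weight, height, BMI, three percentiles, waist, systolic and diastolic pressure), seven glucose and lipid values, and ghrelin, IL-6 and miR-221. 9 + 7 + 3 = 19.
- Species after filtering: not in the protocol. Assumed 100-300.
- True correlation: 0.5, assumed for illustration.

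**Power with Bonferroni over m tests** (Fisher z): power ≈ Φ(atanh(0.5) × √(48 − 3) − z), where z is the two-sided normal critical value at 0.05/m. The first term is 0.5493 × 6.708 = 3.685.

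| Family | m | 0.05/m | z | Power |
|---|---|---|---|---|
| No correction | 1 | 0.05 | 1.960 | 96% |
| One variable × 100 species | 100 | 5.0e-4 | 3.481 | 58% |
| One variable × 300 species | 300 | 1.7e-4 | 3.765 | 47% |
| 19 variables × 100 species | 1,900 | 2.6e-5 | 4.203 | 30% |
| 19 variables × 200 species | 3,800 | 1.3e-5 | 4.357 | 25% |
| 19 variables × 300 species | 5,700 | 8.8e-6 | 4.445 | 22% |

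The approximation is slightly favourable. A simulated Pearson test gives 27% at 2,000 tests and 20% at 5,000, where Fisher z gives 30% and 23%.

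The correlation detectable with 80% power is tanh((z + 0.842)/6.708): 0.64-0.66 for the pooled family, against 0.40 uncorrected.

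**Benjamini-Hochberg at 5%** (simulation, independent tests, m = 3,800, r = 0.5):

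| Share of tests that are real | Benjamini-Hochberg finds | Bonferroni finds |
|---|---|---|
| 1% | 52% | 25% |
| 5% | 72% | 25% |
| 10% | 79% | 25% |
| 20% | 86% | 25% |

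The observed false-discovery rate was 4-5%. With one variable as the family (100-300 tests) and 5-20% real, Benjamini-Hochberg finds about 71-86%, against 47-58% with Bonferroni. The gain shrinks when real associations are few, because the strictest Benjamini-Hochberg threshold is itself 0.05/m.

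**Species compared between arms** (two-sample t test, 24 per arm, 100-300 tests): the difference detectable with 80% power is 1.34-1.44 SD with Bonferroni, against 0.83 SD uncorrected.

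**Ten blood outcomes as one family** (assumed true effects of 0.9 SD, 3-8 of the ten real): Bonferroni 57%, Holm 59-66%.

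**The case against.** **The commitment is conditional and the family undefined.** This stands. The sentence opens with a condition, so the protocol does not bind the analyst to Bonferroni over every species-variable pair. A reader might infer thousands of corrected tests, but that number is not in the document, and a family of one variable against all species is just as ordinary. Pooling also counts near-duplicates as separate tests: weight beside BMI and its percentile, and HOMA beside the glucose and insulin it is computed from. The condition does not remove the problem, however. The only alternative the text leaves is no correction, and 3,800 tests at 0.05 would give up to 3,800 × 0.05 = 190 false positives.

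**The objective is not defeated.** A reader might infer that the microbiota outcome must end with nothing significant. The figures contradict this. With 5-20% of 3,800 tests real (190-760 associations), Bonferroni at 25% still finds about 48-190. Even ten independent true associations give a 1 − 0.75^10 = 94% chance of at least one hit. Ordination, clustering and the regression model also serve the objective and do not depend on this correction. Nor is the correlation screen the treatment comparison.

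**Bonferroni is valid, and the details may sit in an analysis plan that is not shown.** Both are fair. The loss is sensitivity in secondary and exploratory work. But the protocol does name a method, and an analysis plan that follows it would carry that method over.

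**The simulated gain rests on assumptions.** It does: independent tests, a common correlation of 0.5 and an assumed share of real effects. Relative abundances and the chart variables are dependent. The exact gain is therefore uncertain; its direction is not, since at the same 5% level Benjamini-Hochberg rejects everything Bonferroni rejects.

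**Conclusion.** The point holds as a low-priority efficiency gain. It is not an error that invalidates any analysis. For true correlations of 0.5 in 48 children, Bonferroni would miss roughly half the species associations if each variable is its own family, and 70-78% if all 19 variables are pooled. Both figures depend on the assumed 100-300 species. Benjamini-Hochberg would recover more under either family, by an amount that depends on how many associations are real. The Holm gain for the blood outcomes is small, between 2 and 9 percentage points under the assumed effects. The primary BMI z-score test is untouched.

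**What to change.** In the Statistical analysis section, or in the analysis plan before unblinding:

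- Define the species-level families (comparison between arms; correlations with the quantitative variables, stating whether these are pooled or taken per variable).
- Replace Bonferroni in those families by Benjamini-Hochberg at an expected false-discovery rate of 5%, and label the results exploratory.
- Wherever the blood outcomes are corrected as a family, use Holm instead of plain Bonferroni.

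The cost is a change of wording; no data or patients are added. There are two downsides. On average about 5% of the listed species may be false leads; this is an expectation over repeated use and does not cap any one list. Holm also does not directly give the simple simultaneous confidence intervals that Bonferroni does.
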